### Blinding

It is not possible to blind study project staff to the randomisation process, however, the participants will be blinded as to whether they are in the study or control group. The assessor will be blinded until the comparative data analysis is conducted. Participants will be given codes when recruited and these codes will be used throughout the implementation of the study. The participant codes will be revealed only at the six and 12 month comparative data analysis.

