### Recruitment and randomisation process

A stratified random sampling procedure will be adopted to recruit participants from 560 playgroups embedded in 106 suburbs (neighbourhoods) within the Perth metropolitan area. Stratification will be conducted by suburb geographical location and Socio-Economic Indexes For Area (SEIFA) scores. SEIFA scores are values derived from income, education level, employment status and skill level [35]. The suburbs will then be randomly assigned to either the intervention group or the control group using a table of random numbers. Control and intervention group suburbs will be arbitrarily matched for low and medium levels of socio-economic status based on the SEIFA scores. The senior Playgroup WA Inc. staff will make phone calls to all registered playgroup leaders, explain the REFRESH project and obtain permission for project staff to contact the playgroup. Project staff will visit the playgroup to further explain the project, obtain consent and allocate participants to the intervention or control group. Intervention group participants will also complete the Physical Activity Readiness Questionnaire [36] and provide a medical certificate if deemed necessary before commencing the program.

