##### Delivery of intervention in playgroup settings

The intervention will be delivered over six months. Interventions that aim to address multiple risk factors such as nutrition and physical activity show more positive outcomes when multiple intervention strategies are used to reach the target audience [43,47]. Hence the intervention group participants will receive four strategies: face-to-face workshop information and skill development session; mailed or emailed newsletters; SMS reminders on the main messages of the REFRESH program; and a home-based component.

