##### Delivery of face-to-face workshops

The intervention group participants will receive six workshop sessions over six months (one session a month). Each session will be conducted for 30 minutes by project staff during the playgroup session at the playgroup venue. Workshops will focus on enhancing knowledge, attitudes and skills to enable informed decision making about nutrition and physical activity behaviours (Table 1).

**Table 1 T1:** REFRESH Intervention

Session (Week)	Session Details	Participant resources/interactive activities
1 (Week 1)	1. Introduction to Refresh Program 2. Overview of healthy eating and being physically active 3. Focus nutrition: fruits, vegetables and water • Guidelines • Benefits/barriers/overcoming barriers	1. Resources: • Program booklet • Healthy recipe booklet • Session one information summary pamphlet 2. Interactive activity: • Determine participant program needs

2 (Week 5)	1. Focus behaviour change: • Stages of change • Goal setting: long and short term goals 2. Focus physical activity: aerobic • Guidelines • Benefits/barriers/overcoming barriers 3. Focus nutrition: five food groups and 'extra' foods • Guidelines • Benefits/barriers/overcoming barriers	1. Resources: • Pedometer • Family dinner and physical activity planner (fridge magnet) • 'Extra' food record sheet • Session two information summary pamphlet 2. Interactive activity: • Playgroup 10,000 steps per day challenge

3 (Week 9)	1. Focus behaviour change: • Review established short term goals • Set new short term goals 2. Focus physical activity: Muscle strength and flexibility exercises • Guidelines • Benefits/barriers/overcoming barriers	1. Resources: • Muscle strength and flexibility exercise card (fridge magnet) • Physical activity diary • Session three information summary pamphlet 2. Interactive activity: • Muscle strength and flexibility exercises • Integrated exercises "

4 (Week 13)	1. Focus behaviour change: • Review established short term goals • Set new short term goals 2. Focus nutrition: • Healthy eating messages • Menu planning • Food label reading • Making sense of nutritional claims	1. Resources: • Shopping list with healthy shopping tips • Comparing packaged food per 100 g (fridge magnet) • Session four information summary pamphlet 2. Interactive activity: • Reading packaged food labels • Developing a daily menu

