### Control group

The control group participants will not receive any intervention materials. Their only contact with the project will include completing the questionnaires at the three data collection periods.

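### The protocol says participants are blinded to their group, but intervention mothers cannot be, and masking an assessor does not protect self-reported outcomes

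*Protocol article*

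**What the plan says.** The Blinding section makes four statements:

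- Project staff: "It is not possible to blind study project staff to the randomisation process".
- Participants: "however, the participants will be blinded as to whether they are in the study or control group".
- Assessor: "The assessor will be blinded until the comparative data analysis is conducted".
- Codes: "The participant codes will be revealed only at the six and 12 month comparative data analysis".

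Other sections describe what each arm experiences. Under Recruitment and randomisation process, suburbs are assigned at random, and staff then visit each playgroup to "explain the project, obtain consent and allocate participants to the intervention or control group". Under Delivery of intervention in playgroup settings: "Hence the intervention group participants will receive four strategies". Under Control group: "The control group participants will not receive any intervention materials". That section adds that controls' only contact with the project is filling in questionnaires at the three collection points.

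The Outcome measures section collects physical activity, diet, knowledge, self-efficacy, social support and general health by self-administered questionnaire. Height, weight, waist and hip girth are self-reported.

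**The concern.** The sentence on participants concerns a mother's knowledge of her own group. The two arms differ so visibly that this cannot hold for a mother who attends the programme.

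This matters because the mother supplies the outcome data. Intervention mothers spend six months learning guideline targets and setting goals, and then report on those same behaviours. If taking part changes how they report as well as what they do, the comparison mixes the two. A blinded assessor cannot separate them, because no assessor stands between the mother and the recorded answer. A report that repeated the Blinding section would lead readers to rate the risk of bias lower than the design allows.

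A lesser concern is the timing of code release. If labels are opened at the six-month comparison and never closed again, choices about coding and modelling the 12-month data could be made with six-month results by arm already known.

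**Working it through.** The claim contains no figure to reproduce. The check is a comparison of sections.

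**Step 1: what each arm receives**

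| Item (section of the protocol article) | Intervention | Control |
|---|---|---|
| Readiness questionnaire before starting (Recruitment and randomisation process) | yes | not described |
| Pedometer with the baseline and six-month questionnaires (Data collection) | yes | no |
| Workshops (Delivery of face-to-face workshops) | 6 | 0 |
| Newsletters (Delivery of newsletters) | 6 | 0 |
| SMS reminders (Delivery of SMS reminders) | 18 | 0 |
| Home resources (Delivery of home based component) | yes | none |
| Outcome questionnaires (Data collection) | 3 | 3 |

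Scheduled programme contacts over six months are 6 + 6 + 18 = 30 in the intervention arm and 0 in the control arm. The Abstract gives other frequencies for newsletters and SMS. The conclusion does not depend on the exact count, since any version leaves the control arm at 0.

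**Step 2: can an intervention mother be unaware of her group?** Staff explain the project before she consents. She then completes a form that is specified only for her arm, is given a pedometer, and attends sessions of which the first introduces the programme by name (Table 1). No sham or attention programme is described that would make her experience resemble a control mother's. She cannot be unaware that she is receiving the intervention.

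**Step 3: can a control mother be unaware?** Possibly, in part. Assignment is by suburb, so her playgroup need not see the programme. The article does not say whether the explanation at the visit mentions a comparison arm. Her knowledge of her arm is an inference.

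**Step 4: whom does the blinded assessor protect?** The outcomes are self-completed, so an assessor who handles returned questionnaires cannot influence the answers in them. Measured data do not fill the gap. Pedometers go to the intervention arm only, and the staff-measured subsample of 100 (Outcome measures) is drawn from the intervention arm only. Neither can show whether reporting error differs between arms.

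**Step 5: when are the codes opened?** The Blinding section names the six-month and the 12-month comparative analyses, and no section closes the codes again between them. The article does not date the six-month analysis. Study design places both data collection and data analysis in the final year. That 12-month data would still be outstanding at code release is therefore plausible but not stated.

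**The case against.** Lack of participant blinding is unavoidable with a workshop programme. The sentence may also be a clumsy way of saying that suburb-level assignment keeps mothers unaware of the other arm's content. That reading is reasonable for control mothers and limits the point accordingly. A reader might infer that every participant will know her arm, but the article does not establish this for controls. It does not rescue the sentence, which is about knowing one's own group.

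On code release, a reader might infer that nobody is masked for the 12-month data. The documents do not support that. They do not say who receives the codes, they do not date the six-month analysis, and the sentence can be read as keeping each wave coded until its own analysis. The six-month comparison is also the one the trial is sized on, so making it then is legitimate. How far the models are fixed in advance may be settled in an analysis plan that is not shown. This part stands only as a precaution.

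A reader might also express the possible reporting bias as a share of the 0.2 effect. The documents give no size for that bias, so any such share would only restate the range assumed for it.

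Finally, the workshops teach guidelines, goal setting and skills. Nothing suggests that mothers are trained in how to answer the questionnaire. The concern is ordinary differential self-report.

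**Conclusion.** The participant-blinding claim is wrong as written. It fails for intervention mothers on the article's own description, and for control mothers it can mean at most that they may not know what the other arm receives. The assessor-blinding claim may be true, but it gives no protection against differential reporting in self-completed outcomes.

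No numerical bias can be derived from the documents. The consequence is for interpretation: the trial can show an effect on reported behaviour, and its masking should not be presented as a safeguard for that comparison. The conclusion rests on the absence of any described sham programme and on outcomes being collected as the Outcome measures section states.

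Code release at six months is secondary. The text permits it and does not provide for re-masking. Whether it affects the 12-month analysis depends on timing and access that the article does not give.

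**What to change.** - In the Blinding section, replace the sentence on participants with a statement that participants and project staff are not blinded. If wanted, add that control mothers may be unaware of what the other arm receives.
- Limit the masking claim to data entry and analysis under coded arm labels.
- State that outcomes are self-reported and open to differential reporting, and word the conclusions as effects on self-reported behaviour.
- Fix the analysis code for both the six-month and the 12-month comparisons before the six-month labels are revealed, and say who receives the codes.

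The cost is revised wording, a more cautious conclusion and slightly more discipline in the analysis. Sample size, intervention and instruments are unchanged.

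Concealing the arm until the baseline questionnaire is returned is not part of this fix. Only the intervention arm gets a pedometer with that questionnaire, and only that arm is assigned the readiness form. Concealment would work only if both were handed over after the questionnaire came back, which changes the order of baseline procedures and not just the wording.

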### Statistical analysis

Data collected will be coded and analysed using the Statistical Package for the Social Sciences computer statistical software [39]. Descriptive statistics will first be used to summarise participants' demographic and health characteristics. For the hierarchical data (repeated measurements of individuals) collected over the one-year observational period, multi-level repeated measures analyses and multivariate logistic regression analyses will be used extensively in the statistical analyses.

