**Methods/Design:**

The current study is a randomized controlled trial lifestyle (nutrition and physical activity) intervention for mothers with children aged between 0 to 5 years attending playgroups in Perth, Western Australia. Nine-hundred participants will be recruited and randomly assigned to the intervention (n = 450) and control (n = 450) groups. The study is based on the Social Cognitive Theory (SCT) and the Transtheoretical Model (TTM), and the Precede-Proceed Framework incorporating goal setting, motivational interviewing, social support and self-efficacy. The six month intervention will include multiple strategies and resources to ensure the engagement and retention of participants. The main strategy is home based and will include a specially designed booklet with dietary and physical activity information, a muscle strength and flexibility exercise chart, a nutrition label reading shopping list and menu planner. The home based strategy will be supported by face-to-face dietary and physical activity workshops in the playgroup setting, posted and emailed bi-monthly newsletters, and monthly Short Message Service (SMS) reminders via mobile phones. Participants in the control group receive no intervention materials. Outcome measures will be assessed using data that will be collected at baseline, six months and 12 months from participants in the control and intervention groups.

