### Sample size determination

In order to detect a 20% difference in physical activity at 80% power and 5% level of significance, sample size of 310 mothers of young children are required at the 6-months post-intervention survey in each of the intervention and control groups. A small effect size (0.2) [37] is assumed for studies on behavioural effects due to the influence of extraneous variables and the subtleties of human performance. Allowing for an attrition rate of 30%, 900 mothers of young children will be recruited into the study. Sample size calculations were determined using Power Analysis and Sample Size software [38].

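### Suburbs are randomised, but the stated analysis hierarchy stops at the individual mother; if outcomes correlate within suburb, follow-up comparisons between arms will exceed the nominal 5% error

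*Protocol article*

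**What the plan says.** **Allocation.** The protocol article, under *Recruitment and randomisation process*, plans to "recruit participants from 560 playgroups embedded in 106 suburbs (neighbourhoods) within the Perth metropolitan area", and then states: "The suburbs will then be randomly assigned to either the intervention group or the control group using a table of random numbers". This is the only random mechanism described. Suburbs in the two arms are matched on SEIFA level. The same section goes on to say that project staff visit the playgroup, "obtain consent and allocate participants to the intervention or control group". The abstract puts it differently again: "Nine-hundred participants will be recruited and randomly assigned to the intervention (n = 450) and control (n = 450) groups".

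**Delivery.** Workshops are given to groups: "Each session will be conducted for 30 minutes by project staff during the playgroup session at the playgroup venue".

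**Analysis.** The *Statistical analysis* section gives the structure and method in one sentence. It begins "For the hierarchical data (repeated measurements of individuals) collected over the one-year observational period, multi-level repeated measures analyses" and adds that "multivariate logistic regression analyses will be used extensively in the statistical analyses". Neither suburb nor playgroup is mentioned there as a level, a random effect or a cluster for robust standard errors.

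**Sample size.** The section sets "80% power and 5% level of significance, sample size of 310 mothers of young children are required at the 6-months post-intervention survey" in each arm, for an effect size of 0.2. It gives no ICC, no design effect and no sidedness.

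**The concern.** Arm is assigned by suburb, so it varies only between suburbs, and the information about its effect comes from contrasts between suburbs. A random effect for the mother accounts for correlation among her own three surveys. It does nothing for correlation between different mothers in one suburb, or between mothers who attend the same workshops. Suburbs are stratified by location and socio-economic score, and mothers are recruited through shared playgroups, so some similarity in diet and activity within a suburb is plausible.

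If that similarity exists and is left out of the model, the comparison of arms at a follow-up survey has a standard error that is too small, a confidence interval that is too narrow, and a false-positive rate above the stated 5%. The participant-level wording in the abstract adds to the risk, because a reader or analyst could take mothers to be the randomised units.

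**Working it through.** **1. The plan's own figure.** For two means with effect size d, n per arm = 2(z_alpha + z_beta)²/d².
- One-sided 5%, 80% power, d = 0.2: 2 × (1.645 + 0.842)²/0.04 = 309.1, so 310. This matches the stated figure.
- Two-sided: 2 × (1.960 + 0.842)²/0.04 = 392.4, so 393. This does not match.
- Attrition of 30%: 620/0.70 = 886, close to the 900 planned.

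The stated number is therefore reproduced by a calculation for independent mothers, with a design effect of 1. The sample size and the analysis section treat the mothers in the same way. (The sidedness and the missing design effect in the sample size are separate points.)

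**2. Inputs for the clustering check.** From the article: 310 per arm, so 620 mothers at six months; 106 suburbs in the sampling frame. Assumed, because the article does not give them: ICC from 0.01 to 0.10, fewer participating suburbs as an alternative, equal cluster sizes, and a two-sided 5% test.

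**3. Single follow-up comparison.** With m = 620/(number of suburbs), the design effect is DE = 1 + (m − 1) × ICC. If suburb is ignored, the true standard error is √DE times the reported one, and the actual error is 2 × [1 − Φ(1.96/√DE)].

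| Suburbs | m | ICC | DE | √DE | Actual error |
|---|---|---|---|---|---|
| 106 | 5.85 | 0.01 | 1.048 | 1.024 | 5.6% |
| 106 | 5.85 | 0.02 | 1.097 | 1.047 | 6.1% |
| 106 | 5.85 | 0.05 | 1.242 | 1.115 | 7.9% |
| 106 | 5.85 | 0.10 | 1.485 | 1.219 | 10.8% |
| 50 | 12.4 | 0.01 | 1.114 | 1.055 | 6.3% |
| 50 | 12.4 | 0.02 | 1.228 | 1.108 | 7.7% |
| 50 | 12.4 | 0.05 | 1.570 | 1.253 | 11.8% |
| 50 | 12.4 | 0.10 | 2.140 | 1.463 | 18.0% |

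Simulated null trials with one outcome per mother agree: at ICC 0.05, ignoring suburb gave 8.2% with 106 suburbs of 6 mothers and 13.6% with 40 suburbs of 16. Analysing suburb means with a t-test brought the error back to about 5% in every setting.

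**4. Change from baseline.** The plan has repeated measures, so the contrast of interest may be arm by time. Take 60 suburbs of 10 mothers, a suburb variance share of 0.05, and an assumed within-mother correlation of 0.5.
- Suburb effects stable over time: they cancel in the change score, so DE = 1 and the error is 5%.
- Suburb effects drawn afresh at each survey: the suburb variance of the change is 2 × 0.05 = 0.10, and the remaining variance is 2 × 0.95 × (1 − 0.5) = 0.95. The ICC of change is 0.10/1.05 = 0.095, DE = 1 + 9 × 0.095 = 1.86, and the error is 15.0%.

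Simulation of a setting with these suburb numbers gave about 10% on follow-up alone, about 5% on change with stable suburb effects, and about 15% on change with varying effects.

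**The case against.** **The article is condensed.** It does use the term multi-level, and an article commonly leaves random effects to a full analysis plan. This carries some weight: one should not say that the models exclude clustering, only that none is stated. It does not remove the point. The article is not silent on the hierarchy; it says in parentheses what the hierarchy is, and the randomised unit is not in it.

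**Some text points to individual allocation.** The abstract and the phrase about allocating participants could suggest that mothers are randomised. But that phrase comes after suburb assignment and names no second random step. The wording needs reconciling; it does not displace suburb randomisation.

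**The inflation is conditional.** A reader might infer that standard errors are certainly too small, and that every between-arm comparison breaches 5%. The documents do not support this. The inflation needs an ICC above zero, and none is given. With the only suburb count in the article (106) and an ICC of 0.01 to 0.02, the error is 5.6% to 6.1%, which is modest. For change from baseline with stable suburb effects there is no inflation. The larger figures need a higher ICC, fewer suburbs, or suburb effects that vary over time, and the article gives none of these.

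**A suburb random intercept alone is not enough.** This is correct for an arm-by-time contrast: in balanced data, a time-constant intercept leaves its standard error unchanged. The fix has to cover this case.

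**Conclusion.** The point holds in conditional form. The article randomises suburbs, but it fixes a data hierarchy that ends at the mother and states no clustering by suburb or playgroup for either type of model. That mismatch is in the text and needs no assumption.

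Its consequence does need assumptions: correlated outcomes within suburb, a two-sided 5% test, 620 mothers and equal cluster sizes. On these, the actual error of a follow-up comparison runs from 5.6% to 10.8% across ICC 0.01 to 0.10 with 106 suburbs, and from 6.3% to 18.0% with 50. For change-from-baseline contrasts it ranges from none to substantial, according to how stable suburb effects are. Since none of these quantities is known in advance, and the correction is cheap, the analysis should not depend on their being favourable.

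**What to change.** - **Design wording.** Describe the trial as cluster randomised by suburb. Correct the abstract, and reword the sentence on allocating participants so that it says a mother's arm follows from her suburb.
- **Continuous outcomes.** Make suburb a level. Use either a suburb random intercept plus a suburb-by-time random effect in the repeated-measures model, or a suburb random intercept in a follow-up model adjusted for baseline. Cluster-robust or GEE inference on suburb is an alternative.
- **Binary outcomes.** Use logistic models with a suburb random effect, or GEE clustered on suburb.
- **Inference.** Base degrees of freedom on the number of suburbs, and report that number and the observed ICC.
- **Covariates.** Adjust for SEIFA level, on which suburbs are matched; geographical location is optional. A playgroup level is also optional: 620 mothers spread over all 560 playgroups would be only about 1.1 each (620/560).

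This needs a suburb code in the dataset and revised text, with no extra data collection from participants. The downside is somewhat wider, correct confidence intervals.
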